# PROTOCOL TITLE

Operational assessment of laboratory information system for MDR-TB in Lima, Peru

# FUNDING

MIT William Asbjornsen Albert Memorial Fellowship

Office of AIDS Research, National Institute of Health

Bill and Melinda Gates Foundation

# SPECIFIC AIMS

Concisely state the objectives of the study and the hypothesis being tested.

The objective of this study is to compare the effects of a web-based laboratory information system (e-Chasqui) between a network of health establishments with access to e-Chasqui (intervention group) and a network of health establishments without access to e-Chasqui (control group).

The specific aims are:

1. To compare the “laboratory turn-around-time” (from the date a culture or drug susceptibility test (DST) result is obtained to the date the result is obtained at the health center) of samples pertaining to health establishments in the intervention versus the control group.
2. To compare the “clinical turn-around-time” (from the date the DST result is obtained to the date the patient is evaluated by a physician in possession of that result) among MDR-TB patients pertaining to health establishments in the intervention versus control group.
3. To compare the laboratory reporting errors (defined as incorrect smear, culture, or DST results) between health establishments in the intervention versus control group.
4. To qualitatively assess the acceptability and usability of e-Chasqui among users in health establishments with access to the system.

We aim to test the following hypotheses:

1. The laboratory turn-around-time for health establishments with e-Chasqui access will be smaller than that for establishments without e-Chasqui access.
2. The clinical turn-around-time for patients pertaining to health establishments with e-Chasqui access will be smaller than that for patients in establishments without e-Chasqui access.
3. Health establishments with e-Chasqui access will have fewer errors compared to those without e-Chasqui access.
4. Factors associated with acceptability and usability of e-Chasqui by systems users can be identified.

# BACKGROUND AND SIGNIFICANCE

Provide a brief paragraph summarizing prior experience important for understanding the proposed study and procedures.

Delays in starting patients with multi-drug resistant tuberculosis (MDR-TB) on appropriate medication treatment lead to worsened patient outcomes [Telzak et. al, 1995] and increased risk of transmission. In Peru, the National Tuberculosis Program (NTP) has provided treatment for patients with MDR-TB since 1996, with cure rates ranging from 48% to 83% [Suarez 2004; Mitnick 2003]. Nonetheless, significant delays exist in the diagnosis of MDR cases and timely treatment initiation, in particular since MDR-TB treatment has been scaled to a national level.

Our preliminary work has found that the average turn-around-time (TAT) from the request of a DST to the prescription of appropriate treatment was 148 days (4.9 months) [unpublished data]. To address this delay, the NTP and the National Reference Laboratory (NRL) have jointly implemented the programmatic, decentralized use of two rapid DST methods: radiometric BACTEC-460 system and the Griess phenotypic assay method. The implementation of the rapid DST methods is planned as a component of efforts to scale up MDR-TB treatment to achieve nation-wide coverage. The NRL is currently overseeing the process of transferring DST about first-line drugs using the Griess method to seven regional laboratories which currently provide coverage for 90% of the national TB burden. In two of these regions (Lima Este and Lima Ciudad), an observational study “Operational Assessment of Diagnostic Methods for MDR-TB in Lima, Peru,” has been undertaken as a collaborative effort between the Centers for Disease Control and Prevention (CDC), Harvard University, and the Peruvian Ministry of Health, to assess the impact of these two methods in reducing the time to culture conversion among patients with MDR-TB.

Despite these advances, our preliminary work has highlighted the importance of other factors that contribute to the delays in timely diagnosis and management of MDR-TB cases. In fact, a closer assessment of the overall TAT found that there are two time intervals that contributed most heavily to this delay: the time to process a DST (75 days), and the time from DST result to patient re-evaluation (66 days). While the first delay could be addressed by efforts to implement rapid diagnostic methods at the decentralized (regional) level, benefits from such an intervention would be attenuated unless “downstream” factors contributing to TAT delay was also addressed.

For this second delay, an information system could be used to virtually eliminate the time to communicate results between the different institutions. As we have shown in previous studies, systems for managing medical data in the MDR-TB treatment program in Lima are often complex and slow with a significant risk of data errors [Choi et al 2004]. In 2001 we developed and deployed a web based medical record system, the PIH-EMR, to assist in the clinical management of these MDR-TB patients [Fraser et al, 2002]. This system includes a substantial set of data entry and analysis tools for laboratory results including sputum smears, cultures and DSTs. The PIH-EMR can also alert clinicians to abnormal laboratory results either when they login to the system, on specially formatted patient reports, or by email. Over the last six months the PIH-EMR has been modified to support the decentralization of DSTs in the regional laboratories. This laboratory component of the PIH-EMR, termed “e-Chasqui,” permits web-based entry of culture and DST results at all regional and central laboratories performing these tests. In addition, the system includes applications to assess quality control, generate aggregate reports, notify health centers of new results or contaminated samples, and track enrolled patients and the status of pending laboratory tests.

The NTP and the NRL have established a collaborative agreement to integrate e-Chasqui into the current management of patients at risk of MDR-TB. The implementation of e-Chasqui is being currently undertaken in two regions and, if effective, will then be expanded to provide a national network of all laboratories performing DST. It will be unfeasible for us to implement the information system in all health centers simultaneously because of the intensive initial demands on resources and training. Therefore, the implementation of the information system will occur in stages. For each region, necessary infrastructure and training to use the information system (including internet access, computers, and training on data security and patient confidentiality, and the use of email and the information system) will occur in a stepwise process, first involving approximately one half of the participating health establishments and then involving the remaining half.

Because of this staged nature of “roll-out,” there will be a period of time during which only half of the health establishments will be using the information systems. During this period, we will conduct **Part A** of our study, comparing our study endpoints among those health establishments with access to the information system (the intervention group), and those without access (at that time) to the information system, the (simultaneous control group). Given our logistical and financial constraints, which make simultaneous implementation of this programmatic intervention unfeasible, and given the programmatic agreement to eventually implement the information system in all health establishments, we do not feel that this strategy for implementation or this study design is unethical. Afterwards all health establishments will gain access to the information system. **Part B** of the study will compare the same endpoints among health establishments with initial access to the information system (intervention group) to those endpoints in the same health establishments before they gained access to the information system (historical control group). This study is therefore a prospective observational study designed to measure the impact of this programmatic intervention.

The operational assessment of this informatics intervention will be essential to determine if the system is effective in reducing delays in the management of suspected MDR cases and therefore, whether the system should be implemented at the national level. It will assess the impact of e-Chasqui on reducing reporting delays and laboratory data errors, and improving patient outcomes. More broadly, this study would provide data on a critical research question in medical informatics: whether the use of information systems can be shown to improve quality of patient care. Few studies have been able to convincingly demonstrate such benefits in the US and virtually none in developing countries. By using the data being collected by the overarching study “Operational Assessment of Diagnostic Methods for MDR-TB in Lima, Peru,” this proposal offers a unique opportunity to assess the clinical effects of improving information flow.

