# Study endpoints

The following primary endpoints of this study are:

1. Median “Laboratory turn-around-time” (from the date a culture or drug susceptibility test (DST) result is obtained to the date when the result is obtained at health center).
2. Median “Clinical turn-around-time” (from the date the DST result is obtained to the date the patient is evaluated by a physician).
3. Percent laboratory errors, by type (see Appendices: Quality Control Form) of error for health establishments in the intervention versus the control group.
4. Qualitative assessment of the acceptability and usability of e-Chasqui among users in health establishments with access with to the system.

Secondary endpoints of this study will include

1. Reduction of patients with delay above 100 days between the date an MDR result was obtained to the treatment start date of an MDR-TB regimen
2. Reduction of patients with delay above 100 days between the date an MDR result was obtained and the date of change to an appropriate regimen based on the DST result [would only use MDR results for these endpoints because we have more possibility to intervene]
3. Reduction of time to resend a sample when the first sample is found to be contaminated (from date of test result found to be contaminated to date of request of second sample)
4. Approximate cost of the intervention as a whole and per patient

The cost effectiveness analysis of this information system will be included in a larger cost effectiveness study planned for the overarching study, “Operational Assessment of Diagnostic Methods for MDR-TB in Lima, Peru.”

#

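### Part A is bounded only by roll-out status, so control intervals still open when the control establishment gains e-Chasqui bias raw medians and proportions towards no difference

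*Protocol*

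**What the plan says.** Background and Significance describes a two-stage roll-out. Part A is conducted while "there will be a period of time during which only half of the health establishments will be using the information systems". Its controls are "those without access (at that time) to the information system", so control status is temporary by design. The section continues: "Afterwards all health establishments will gain access to the information system". Research Design and Methods makes Part A the primary design and Part B, the before-and-after comparison within first-wave establishments, the secondary one.

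The endpoints at issue, under Study endpoints, are intervals. Primary endpoint 2 is a median time "from the date the DST result is obtained to the date the patient is evaluated by a physician". Secondary endpoint 1 reads "Reduction of patients with delay above 100 days between the date an MDR result was obtained to the treatment start date" of an MDR-TB regimen, and secondary endpoint 2 applies the same threshold to the change to an appropriate regimen. From preliminary work, Background and Significance puts the baseline time from DST result to re-evaluation at 66 days, as one component of an average total of 148 days. No spread or median is given.

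The visible text gives no length for Part A. It refers to a study schema that is not reproduced.

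**The concern.** A control patient whose result is dated shortly before the control establishment gets e-Chasqui starts the interval without the system and may finish it with the system. Contamination is plausible on the protocol's own account. The system "permits web-based entry of culture and DST results at all regional and central laboratories performing these tests", and it notifies health centres of new results and tracks pending tests. A result still outstanding at a control site could therefore become visible there on the day access starts (an inference, not a statement in the protocol).

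A raw median or proportion leaves two simple ways to treat such an interval, and both favour no difference:

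- **Followed to its end and counted as control.** The control group is credited with some of the intervention's benefit.
- **Kept only if completed within the period.** Long delays are cut off, and more of them are lost from the slower group.

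Part B has the same gap at the first go-live, where historical intervals may still be open. The protocol says the assessment will inform whether the system should be implemented nationally, so an understated effect matters.

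**Working it through.** The protocol gives no figure for this contamination, so there is none to reproduce. Its delay figures are coherent: 75 + 66 = 141 of the 148 days, and 148/30.44 = 4.86 months (stated as 4.9).

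**Inputs.** From the protocol: mean delay m = 66 days and the 100-day threshold. Assumed: results arrive uniformly over a Part A of length T = 90, 180, 365 or 730 days; delays are exponential; e-Chasqui multiplies the re-evaluation rate by h = 1.5, 2 or 3; every control interval open at the switch is sped up by h at once. The above-100-day figures use the re-evaluation delay as a stand-in, because no baseline is given for time to MDR treatment start or regimen change.

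**Step 1: share of control intervals open at the switch.** This is (m/T)(1 − e^(−T/m)). For T = 180: (66/180)(1 − e^(−2.727)) = 0.343.

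**Step 2: straddling intervals followed and counted as control.** For t ≤ T the control survival curve becomes

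S(t) = (1 − t/T)e^(−t/m) + [m/((h − 1)T)](e^(−t/m) − e^(−ht/m)).

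For t > T, which is needed only for T = 90 at 100 days, it is [m/((h − 1)T)]e^(−ht/m)(e^((h−1)T/m) − 1).

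Worked case, T = 180 and h = 2:

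- *Median.* The true control median is 66 ln 2 = 45.7 days and the e-Chasqui median is 22.9, a difference of 22.9 before rounding of the medians. S(t) = 0.5 at t = 41.7, so the observed difference is 18.8, a loss of 18%.
- *Above 100 days.* True control 0.220, e-Chasqui 0.048. S(100) = 0.444 × 0.2198 + 0.367 × (0.2198 − 0.0483) = 0.161. The difference falls from 0.171 to 0.112, a loss of about 35%.

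**Step 3: only completed intervals kept.** The delay density is then proportional to (1 − x/T)e^(−x/m). For T = 180 and h = 2 the medians are 29.0 and 18.5 days. The difference is 10.5 instead of 22.9, a loss of 54%.

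**Results, ranges over h = 1.5 to 3:**

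| Part A length | Control intervals open at switch | Loss in median difference, straddlers followed | Loss in above-100-day difference, straddlers followed | Loss in median difference, completed only |
|---|---|---|---|---|
| 90 days | 55% | 29–35% | 62–79% | 74–83% |
| 180 days | 34% | 16–21% | 31–40% | 49–59% |
| 365 days | 18% | 8–11% | 15–20% | 25–32% |
| 730 days | 9% | 4–6% | 8–10% | 12–16% |

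**Sensitivity.** Gamma or lognormal delays with the same mean give 58–62%, 34–36%, 18% and 9% open at the switch. An assumed mean of 100 days gives 66%, 46%, 27% and 14%.

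**Step 4: does censoring repair it?** In simulation with T = 180, censoring control intervals at the switch and taking the Kaplan-Meier median returns the true 45.7 days. The share of control intervals still under observation at 100 days is (1 − 100/T) × 0.2198: none at T = 90, 9.8% at 180 and 16.0% at 365. The 100-day estimate is therefore weak when Part A is short, and unobtainable if it lasts less than 100 days.

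**The case against.** **A last result date or a censoring rule may sit in a statistical analysis plan, and the schema may give the period lengths.** This is fair, and the absence of such detail is not the point. What the protocol itself fixes is a window set by roll-out status together with endpoints framed as raw medians and counts, and that combination produces the bias. Knowing the length would settle its size but not how straddling intervals are treated.

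**The two biased readings are not the only ones.** Controls are defined by lacking access at the time, so censoring at access fits the text. This stands, and it is the remedy proposed here. The protocol also plans monthly data collection and nowhere tells anyone to discard unfinished intervals, so the completed-only column shows what to avoid, not what is planned.

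**The model overstates contamination.** A control result that had already reached its health centre has passed the step e-Chasqui mainly shortens, yet the model speeds up every open interval. This stands: the followed-as-control figures are upper bounds for the assumed hazard ratios. The documents do not say how many results would still be uncommunicated at the switch.

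**A reader might infer that clinical delays are known to run from 66 to beyond 100 days and that serious dilution is therefore certain.** The documents do not support this. The 66 days is a single baseline figure, and the 100 days is a threshold in two secondary endpoints, not an observed delay. With a two-year Part A the median difference would lose only 4–6% if straddlers were followed.

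**Conclusion.** The concern holds in a limited form. With temporary controls and interval endpoints, some control intervals must straddle the switch, and raw medians or proportions are then biased towards no difference. Within the model, the loss in the primary median difference when straddlers are followed ranges from about a third for a 90-day Part A to about 5% for 730 days. Secondary endpoints 1 and 2 are hit roughly twice as hard. Keeping only completed intervals is worse at every length.

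These sizes rest on an assumed Part A length, uniform result dates, exponential delays of mean 66 days, a hazard ratio of 1.5 to 3 and, for straddlers followed as control, immediate speed-up of every open interval. The direction does not depend on the length; the importance does. Laboratory turn-around-time is not quantified, because no separate baseline is given for it, and neither is Part B. The documents do not show that the study would miss a real effect, only that its estimate would be too small by an amount that recording access dates and censoring would avoid.

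**What to change.** - State the planned length of Part A and define its cohort by result date in both groups.
- Record the date on which each establishment gains access.
- Censor control intervals still open at that date, and the matched intervention intervals at the same calendar date.
- For clinical turn-around-time report Kaplan-Meier medians, and for secondary endpoints 1 and 2 the Kaplan-Meier proportion still waiting at 100 days, in place of raw medians and proportions.
- In Part B, censor historical intervals still open at first-wave go-live.
- Do not drop incomplete intervals. Do not exclude every result from the last 100 days of Part A either: with uniform arrival that would remove all control results at 90 days, 100/180 = 56% at 180 and 100/365 = 27% at 365.

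The cost is protocol wording and a log of access dates; no new patient data are needed. Censored intervals lose a little precision. If Part A turns out short, the 100-day proportion will be poorly estimated or not estimable, and the report should say so.

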# RECRUITMENT PROCEDURES

Explain in detail the specific methodology that will be used to recruit subjects at the Partners performance sites, specifically how, when, where and by whom subjects are identified and approached about participation. Provide details of remuneration, if applicable. Include any specific recruitment methods used to enhance recruitment of women and minorities.

The population for this study will be that of the overarching study. Their study population includes those individuals with pulmonary TB who have a risk factor for MDR-TB in the region of Lima Ciudad. Risk groups for MDR-TB are defined by the NTP norms for TB management, and are described in the overarching study protocol. The enrollment procedures for the study are described below.

The treating physician at the health establishment is the primary care giver for all patients with suspected or confirmed tuberculosis. At the time of TB diagnosis or during treatment, the treatment physician may identify a risk factor for MDR-TB. In such cases, a sputum sample is sent to the regional laboratory for DST, using a rapid method (a colorimetric nitrate reductase assay termed the Griess) to identify resistance to isoniazid and rifampicin.

Because all sputum samples of patients who have at least one MDR-TB risk factor will be sent to the regional laboratory for DST, subjects eligible for the study will be identified by this referral. The regional laboratory will contact our study team when an eligible subject has been identified; in addition, the study team will visit each regional laboratory on a weekly basis to review sample referrals and confirm that all eligible subjects have been identified.

Faulty enrollment through this method could occur through two means. First, the treating physician may incorrectly solicit a DST in a patient without an MDR risk factor; second, the care provider may fail to identify a patient with a MDR risk factor. For this reason, the study team will make weekly visits to each health establishment in the study region to review patient medical records. They will 1) confirm that all enrolled subjects have an appropriate MDR-TB risk factor, and 2) identify any subjects who are eligible for the study (i.e. have an MDR-TB risk factor) and have not been previously captured. If any such “missed” subjects are identified, the patient’s status will be discussed with the health establishment to confirm that the patient is being managed as per NTP norms. If the patient has received less than two weeks of TB treatment since identification of one of the above risk factors, then the patient will still be eligible for inclusion into the study.

Since this an observational study of a programmatic intervention, there will be no contact between study investigators and subjects. Therefore, subjects will not be recruited for participation in the study.

# CONSENT PROCEDURES

Explain in detail how, where and by whom consent is obtained and the timing of consent, i.e., how long subjects will be given to consider participation. In general, informed consent is to be obtained by a licensed physician investigator if outside the research realm consent would be obtained usually by a licensed physician. If subjects are unable to give consent due to age (minors) or current physical/mental condition, indicate from whom consent will be obtained, e.g., parent(s), legally authorized representative, next-of-kin, etc. If subject is unable to give consent, describe how subject's ability to consent will be assessed during the trial and how consent will be obtained in the event the subject regains ability to give own consent.

The consent procedures for the overarching study “Operational assessment of diagnostic methods for MDR-TB in Lima, Peru” are described below.

Informed consent will not be sought for data collection, for the following reasons:

1) Patients will not be put at risk by their participation in the study. The data collection process will require no contact with the patients, since the information will be abstracted from patient charts and lab records, and will only include information that is routinely collected in the course of providing clinical care to patients. Moreover, the treatment regimens and management strategies for patients will be determined by the standards of care in vigor in Peru at the time.

2) Participation in the evaluation will not adversely affect the rights and welfare of the subjects. Participation in the evaluation will be determined by the patient's risk of MDR-TB, and will have no impact on the diagnostic method or treatment that the patient receives during or after the evaluation period. The investigators will have no contact with the physicians treating the patients. Patients in the evaluation will be treated no differently than they would were the evaluation not conducted.

3) Seeking patients' informed consent before including them in the evaluation would not be practical for this study. Patients who refuse to participate in this study may be more likely to have MDR-TB or other causes of stigma (e.g. household contact with MDR-TB, HIV). Most MDR-TB patients in Peru reside in illegal and unstable conditions. It would therefore be impossible to obtain informed consent from all patients whose inclusion in the evaluation is crucial. For the same reason, no attempt will be made to provide patients with additional information after the study is completed.

4) Patient confidentiality will be maintained (see Privacy protection below).

